### Telephone calls during 3-month and 6-month periods

Participants in the intervention group will receive a telephone call every 2 weeks during the intervention period and once a month during the follow-up period. Calls aim to support participants’ use of HEAL ABC resources to facilitate behaviour change by reviewing participants’ goals for desired behaviour change. The structure of the telephone calls will be informed by motivational interviewing [33], with the interviewer trained in motivation interviewing technique. The interviewer will explore participant’s own ability to identify the most appropriate plan for their action and explore their strengths and capabilities to change. Guidance will be provided to participants in order to set new goals if satisfactory changes were initiated. The telephone calls will be audio-recorded with an encrypted voice recorder to enable the monitoring and reviewing of the calls and evaluation of the intervention fidelity [34].

### Control (HEALTH group)

Participants allocated to the control group will be referred to the healthy lifestyle recommendations available at the World Cancer Research Fund, Bowel Cancer UK and UK government websites. No additional support or telephone calls will be provided.

### Assessment and outcomes

Both intervention and control group are assessed at baseline, 3- and 6-month data collection points. The schedule of enrolment, interventions and assessments is presented in Table 4.

**Table 4 Tab4:** Schedule for measurement, testing and assessment at baseline and follow-up assessment

Measure/assessment	Method of assessment	Prior baseline	Baseline	Post intervention 3 months	Follow-up 6 months
Enrolment	-	✓	x	x	x
Eligibility screen	-	✓	x	x	x
Informed consent	-	✓	x	x	x
Allocation	-	x	✓	x	x
Participants’ characteristics	Sociodemographic questionnaire	x	✓	x	x
Patients’ medical history	Medical records	x	✓	x	x
Anthropometry	Scale, tape measure, stadiometer	x	✓	✓	✓
Body composition	BIA, CT scans analysis	x	✓	✓	✓
Dietary assessment	3-day food diary, 24 dietary recall	x	✓	✓	✓
Physical activity level	GPAQ Questionnaire	x	✓	✓	✓
Step count	Pedometer	x	✓	✓	✓
Behaviour/motivation	HAPA questionnaire	x	✓	✓	✓
Participant’s experience	In-depth interviews	x	x	✓	✓
Quality of life	SF-12 questionnaire	x	✓	✓	✓
Participants’ contact with healthcare services	Healthcare Resource Use Questionnaire	x	x	x	✓
Morbidities, mortality	Medical records	x	x	x	✓

*BIA* bio-impedance analysis, *CT* computer tomography, *GPAQ* Global Physical Activity Questionnaire, *SF-12* Short form 12 quality of life

### Baseline assessment

At baseline, details of patients’ characteristics will be collected using a sociodemographic questionnaire (see Additional file 1). Patient medical records will be used to collect information on cancer staging using the Classification of Malignant Tumours (TNM classification) post-surgery [35], type of chemotherapy/radiotherapy, disease site and operation details.

Further baseline measurements will include anthropometry, body composition, dietary intake, physical activity, quality of life, behaviour change assessment and blood tests.

#### Anthropometry and body composition

Standard operating procedures will be used to ensure consistency of the measurements. Height will be measured using a stadiometer and records rounded to the nearest centimetre (cm) (Harpenden pocket stadiometer Practical Metrology, Sussex, UK). Body weight will be recorded to the nearest 0.1 kg. Body composition will be measured using bioelectrical impedance analysis (DC-430 MA, Tanita Europe BV, the Netherlands) to assess fat mass and fat-free mass. We will collect copies of computer tomography (CT) scans for participants taken at the closest date to our assessment. The CT scans will be analysed using Slice-o-Matic (Tomovision 5.0, Canada) and Image J (ImageJ, US National Institutes of Health, Bethesda, MA, USA) software. Single axial images at the level of the third lumbar vertebrae will be used to measure total skeletal muscle and total fat mass at the cross-sectional area. Hounsfield units (HU) threshold will be set at − 190 to − 30 for subcutaneous fat, − 150 to − 50 for visceral fat, − 190 to − 30 for intramuscular fat and − 29 to 150 for skeletal muscle. The skeletal muscle area will be normalised for stature by calculating the skeletal muscle index. Muscle mass and fat mass will be calculated using standard equations [36].

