### Recruitment and consent

Participants will be recruited from outpatient CRC surveillance clinics in Great Manchester (Fig. 1). In the hospitals, appropriate participants will be identified from clinical records and screened by clinic staff. A record of people approached and individuals that express an interest will be kept. A patient information sheet and researcher contact details will be provided to facilitate follow up of potentially interested participants. The COVID-19 pandemic in UK in 2020 may preclude using this face to face approach, in which case an alternative non-face to face method of recruitment will be adopted. Participants who are interested in taking part will be consented, randomised and allocated to one of two trial arms. Baseline data will be collected following randomisation to the control or intervention arms.

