#### Biochemistry and haematology

Blood test results of routinely collected inflammatory markers (C-reactive protein, leukocytes level, albumin, haemoglobin) will be collected from patient’s medical records [50].

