### Post-intervention assessment at 3 months

At 3 months, all baseline measurements will be repeated. In addition, a subset of 12 to 15 participants in the intervention group will be interviewed using qualitative interviews. The interviews will aim to gain an insight into participants’ experience of being in the study, using HEAL ABC resources, and will explore motivations, barriers and facilitators regarding adherence to the intervention. A subset of 12 to 15 participants in the control group will also be interviewed about the experience in the study, their level of motivation and action taken towards a healthier lifestyle.

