### Follow-up assessment at 6 months

At 6 months, all baseline measurements will be repeated, and qualitative interviews will be performed again with the same subset of participants. Additionally, cancer recurrences, morbidities and survival will be collected from patients’ medical records and health resource questionnaire provided.

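### CT body composition is scheduled at three visits, but scans are picked by nearest date with no window and no bar on reuse, so one scan may stand for two or three visits

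*Protocol article*

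**What the plan says.** Under Assessment and outcomes, the article states: "Both intervention and control group are assessed at baseline, 3- and 6-month data collection points". In Table 4 the body composition row, with method "BIA, CT scans analysis", is ticked at all three points. The follow-up sections agree: "At 3 months, all baseline measurements will be repeated" and "At 6 months, all baseline measurements will be repeated".

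The study does not take its own CT scans. Anthropometry and body composition gives the source and the selection rule: "We will collect copies of computer tomography (CT) scans for participants taken at the closest date to our assessment". No permitted gap is stated, nor whether the scan must come before or after the visit, nor whether one scan may be used again at another visit. The interval between routine scans is not stated either.

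Two further statements bear on the point. Recruitment and consent says: "Baseline data will be collected following randomisation to the control or intervention arms". Biochemistry and haematology says: "Blood test results of routinely collected inflammatory markers (C-reactive protein, leukocytes level, albumin, haemoglobin) will be collected from patient’s medical records". The bloods are named as a baseline measurement and so fall under the instruction to repeat everything. They have no date rule and no row in Table 4.

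**The concern.** A nearest-date rule returns an image for every visit whenever the participant has any scan on record. Unless routine scans come about as often as study visits, the same image will be nearest to more than one visit. The CT change between those visits is then zero by construction, whatever happened to the participant. The rule also works in both directions, so the scan labelled as baseline may have been taken during the intervention or after it.

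Two stated uses of the data are at stake. Under Outcomes, completeness is judged for every outcome measure at every time point, and means and SDs of change are to support the sample size of a future trial. The abstract lists body composition among the data whose collection is being tested. If the rule fills every cell, the trial cannot show whether a CT measure at 3 months is obtainable.

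**Working it through.** **Inputs from the article.** Visits at 0, 3 and 6 months; intervention period 3 months; nearest-date selection with no other restriction.

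**Plan's own figure.** The article gives no figure on scan timing. Its only sample-size figure is 72 recruited for 60 completers with 15% dropout: 60 / 0.85 = 70.6, which rounds up to 71, or 72 with equal arms. It does not depend on this point.

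**Assumptions.** Routine scans come every T months, with a phase that is random relative to the visits. Earlier and later scans are both available when the selection is made. T is not in the article and is shown as a range.

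**Formulas** (they agree with a simulation of 400,000 draws per T):
- One scan nearest to both 0 and 3 months: max(0, 1 − 3/T). At T = 12: 1 − 3/12 = 0.75.
- One scan nearest to all three visits: max(0, 1 − 6/T). At T = 12: 1 − 6/12 = 0.50.
- Baseline scan dated after the baseline assessment: the offset of the nearest scan is uniform from −T/2 to +T/2, so 0.50 at every T.
- Baseline scan more than 3 months after the assessment, and so after the intervention period: max(0, 1/2 − 3/T). At T = 12: 0.50 − 0.25 = 0.25.
- At least one adjacent pair of visits sharing a scan: twice the first quantity minus the second. At T = 4: 2 × 0.25 − 0 = 0.50. At T = 12: 2 × 0.75 − 0.50 = 1.00.

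| T (months) | Same scan, 0 and 3 | Same scan, all three | Any adjacent pair shared | Baseline scan after assessment | More than 3 months after |
|---|---|---|---|---|---|
| 3 | 0% | 0% | 0% | 50% | 0% |
| 4 | 25% | 0% | 50% | 50% | 0% |
| 6 | 50% | 0% | 100% | 50% | 0% |
| 9 | 67% | 33% | 100% | 50% | 17% |
| 12 | 75% | 50% | 100% | 50% | 25% |
| 24 | 88% | 75% | 100% | 50% | 38% |

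The columns overlap and must not be added. At T of 6 or more, everyone whose baseline scan falls after the baseline assessment is already among those sharing one scan for 0 and 3 months.

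**If only earlier scans were eligible.** Suppose the rule is read as the most recent scan before each visit. Baseline scans could then no longer fall after the assessment. The last scan before month 0 and the last before month 3 would still be the same unless a scan fell in those 3 months. That leaves the chance of sharing at 1 − 3/T, so the reuse problem does not depend on the two-directional reading.

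**Pairs that do not share a scan.** Their two scans are consecutive routine scans, so they lie a full T months apart, not 3. At T = 12, 75% of pairs would show a gap of zero and 25% a gap of 12 months. The average gap is 0.25 × 12 = 3 months, yet no pair measures a 3-month change.

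**The case against.** The case against has five parts.

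**Unknown interval.** The article gives no scan frequency, and with 3-monthly scans nothing is shared. This stands. The text supports saying that changes may be zero for an unknown share of participants, not that they are.

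**Direction of error.** A reader might infer that CT change will be near zero and its SD understated. The documents do not support this. Take T = 12, where 25% of pairs are 12 months apart:
- Mean: under steady drift it is unaffected (0.25 × 12 / 3 = 1). If change starts at month 0 and continues linearly, about 62% of it is kept. If change is complete by month 3, 25% is kept.
- SD, with mean change zero: it doubles if people differ in slope (√(0.25 × 144 / 9) = 2), is unchanged for a random walk (√(0.25 × 12 / 3) = 1), and halves only if the variance of change ignores elapsed time (√0.25 = 0.5).

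Neither size nor direction can be fixed.

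**Bloods and baseline timing.** The nearest-date rule is stated for CT only. For bloods the article names a source and no date rule, so reuse is possible but not prescribed. All baseline data are collected after randomisation in any case; the CT rule adds an unlimited delay. Both corrections stand.

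**Condensed article.** Standard operating procedures are mentioned and the full protocol is not shown, so windows may exist there. That would answer a complaint about missing detail. Here the article states a rule, and that rule cannot be relied on to deliver the three timed measurements in its own schedule.

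**Low materiality.** There is no hypothesis test, CT is not among the outcomes singled out for effect sizes, and bioelectrical impedance is measured directly at each visit. This limits the weight of the point. It does not remove it: impedance is used for fat and fat-free mass, while the visceral fat and skeletal muscle areas come from CT alone.

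**Conclusion.** The point holds for CT. As written, the selection rule allows one image to serve two or three scheduled visits and allows a baseline image from well into the intervention or after it. Nothing else in the article prevents either.

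The chance of a shared baseline and 3-month scan runs from 0% with 3-monthly scans to 75% with 12-monthly scans. About half of baseline scans would fall after the baseline assessment at any interval. These figures assume regular scans at random phase and that later scans are eligible.

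Two consequences follow where scans are shared or late. CT means and SDs of change would not represent 3- or 6-month change, by an amount and in a direction that cannot be stated. CT completeness at each time point would be overstated, which matters most because collectability is what the trial examines. The planned 72 participants and the directly measured outcomes are unaffected. Undated routine bloods are a secondary point. The change is worth making because it is cheap, but the measure is not central to the trial.

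**What to change.** Replace the nearest-date wording with a dated rule:

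- The baseline scan is dated on or before the start of intervention, within a stated window.
- Each follow-up scan falls in a stated window around its visit.
- Each scan is used for one time point only.
- Anything else is missing and is counted as missing in the data-completion rate.
- Scan-to-visit gaps are reported by arm.

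If routine imaging cannot supply a scan at 3 months, remove CT from the 3-month column of Table 4. Apply the same dating and one-result-per-visit rule to the routine blood results.

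The cost is a wording change and the logging of scan and sample dates, with no additional scans. The downside is that CT and blood completeness will look lower; that lower figure is the one a future trial needs.

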#### Dietary assessment

Diet will be assessed using a 3-day food diary and electronic dietary recall. Participants will complete a food diary prospectively during the day and enter all foods and drinks consumed into an online system for dietary assessment, INTAKE24 [37], at the end of each day. INTAKE24 is a self-completed online 24-h dietary recall compliant with the general data protection regulation (2018). To complete the dietary recall, participants will be assigned a specific number, which they receive by email. This will serve as a log enabling access to the online dietary record. Participants will be instructed how to complete a food diary and INTAKE24 recall by the researcher, who is a qualified nutritionist. Data collected will be used to assess energy and nutrient consumption, as well as, frequency of fruit and vegetables, red meat, processed meat, fast food, sugary drinks, sweets, and alcohol. This method of food frequency assessment will replace a standard food frequency questionnaire, which is subjected to reporting error due to the inaccuracy of absolute nutrient values, variation of nutrient values depending on questionnaire length and structure and lack of details recorded about food consumed [38, 39]. Further advantages of combining food diary and electronic recall relate to participant’s age and memory capacity, as the average age of CRC survivors is above 65 years. In addition, a Diet Quality Index will be calculated based on data collected [40].

#### Physical activity level

The Global Physical Activity Questionnaire (GPAQ) will be used to assess participant’s level of physical activity [41]. A validated pedometer will be used [42, 43] to measures daily steps for a week at each time point. Participants will be instructed to wear the pedometer during the day clipped to their waistband on either the left or right hip.

#### Quality of life

Health-related quality of life will be assessed using the SF-12 questionnaire [44], selected for its validity, generalisability and simplicity [45, 46].

#### Behaviour change

Behaviour change will be assessed using a behaviour change questionnaire, using questions derived from the HAPA. This questionnaire was developed to explore changes in different HAPA constructs (aspects related to participant’s behaviour). The HAPA questionnaire has been previously used to investigate changes in HAPA constructs in lifestyle interventions [47–49].

#### Biochemistry and haematology

Blood test results of routinely collected inflammatory markers (C-reactive protein, leukocytes level, albumin, haemoglobin) will be collected from patient’s medical records [50].

### Post-intervention assessment at 3 months

At 3 months, all baseline measurements will be repeated. In addition, a subset of 12 to 15 participants in the intervention group will be interviewed using qualitative interviews. The interviews will aim to gain an insight into participants’ experience of being in the study, using HEAL ABC resources, and will explore motivations, barriers and facilitators regarding adherence to the intervention. A subset of 12 to 15 participants in the control group will also be interviewed about the experience in the study, their level of motivation and action taken towards a healthier lifestyle.

### Follow-up assessment at 6 months

At 6 months, all baseline measurements will be repeated, and qualitative interviews will be performed again with the same subset of participants. Additionally, cancer recurrences, morbidities and survival will be collected from patients’ medical records and health resource questionnaire provided.

#### Healthcare Resource Use Questionnaire

A health economics questionnaire will be used to find out about patient’s contact with primary and secondary healthcare services. The questionnaire was developed by a health economist for the European Union funded project “PreventIT” [51].

### Qualitative interviews at 3 and 6 months

We will aim to recruit participants for interviews until data saturation is achieved and we anticipate this will be between 12 and 15 participants [52]. Overall, this will provide 24–30 interviews in total, and 12–15 interviews at each time point is considered to be sufficient to reach data saturation as recommended by Guest et al. [53]. Participants will be selected at baseline, as the first 12 to 15 who agree to be interviewed. This will allow an early evaluation of participants’ experience of the study. A topic guide developed for the study will be used to conduct the interviews. The guide will cover topics such as experience of randomisation, intervention, HEAL ABC resources and data collection. It will also discuss motivation, barriers and facilitators for following the HEAL ABC intervention. The topic guide will be continually reviewed throughout the interview process to ensure it covers any emerging topics of interest. Interviews will be audio-recorded using an encrypted audio recorder and will be fully transcribed verbatim.

### Outcomes

Outcome related to feasibility will be assessed by adherence to WCRF/AICR guidelines, recruitment rates, retention rates, data completion rates and loss to follow up. Adherence to intervention will be assessed as adherence to the WCRF/AICR guidelines by using a scoring system for nutrition and physical activity guideline adherence developed by McCullough and colleagues [54, 55]. We will also assess number of goals set and number of changes implemented in everyday life during the 3-month intervention. Recruitment rates will be assessed as a cumulative recruitment against target rate each month and retention rates calculated as the number of participants who completed the study divided by the number of participants randomised. Acceptability of the intervention will be explored qualitatively through interviews with a subset of the study participants. Data completion rates will be judged as percentage of missing data and completeness of data for all outcome measures at all the time points. Changes in means and standard deviation will be compared to allow for the sample size calculation for a future trial.

Other outcomes include assessing the practicality of data collection for dietary intake, physical activity levels, behaviour change in relation to diet and physical activity and determining effect sizes for these outcomes. Interviews will be performed to explore participants’ experience, motivation, barriers and facilitators to use HEAL ABC resources and follow the intervention.

In the future, a fully powered RCT will test the efficacy of the intervention alongside outcomes collected in the feasibility trial.

### Sample size

We plan to complete the study with 60 participants allowing for up to 15% drop out over 12 months so will recruit a total of 72 participants. This is based on drop out data identified in a systematic review of the literature [8]. As this study does not aim to test a hypothesis, we follow recommendations for feasibility studies by Lancaster et al. [56].

### Randomisation

Participants will be randomised into control and intervention groups using the sealedenvelope.com [57] block randomisation. The randomisation will be stratified for hospital site and cancer site (colon or rectum). An independent person outside of the research team will generate the allocation sequence and assign participants into their groups. Participants cannot be completely blinded to the intervention but effort was taken to blind differences between HEAL and HEALTH group for participants through the provision of written materials and following the same assessment. The researcher will not be blinded to the intervention and outcomes.

### Statistical analysis

Quantitative data will be analysed using descriptive statistics displayed with 95% confidence intervals. Changes in outcomes between the intervention arm and control, estimate parameters using means and standard deviations will be descriptively compared and will inform a sample size calculation for a full RCT. All quantitative data will be analysed in STATA 15 (StataCorp, TX: StataCorp LLC) [58].

Qualitative interview transcripts will be managed using NVivo 12 software (QSR International Pty Ltd., Doncaster, VIC, Australia) and analysed using the five stages of framework analysis [59]: familiarisation, developing a thematic framework, indexing, charting and mapping and interpretation. During the first stage (familiarisation) the researcher will become immersed in the data, by reading and re-reading the transcripts. Next, a thematic framework will be developed. After this, transcripts will be indexed (coded) line by line using the thematic framework but remaining open to new themes that emerge. Next, the data will be entered into a chart, so that coded extracts can be attributed to individual participants. Finally, participants’ views will be compared and contrasted, and the data presented schematically (mapping). Contrasting explanations will be explored.

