## Methods/design

This is a feasibility parallel group RCT using 1:1 randomisation*.* The study follows CONSORT guidelines for reporting a pilot or feasibility trial [27] and follows the Standard Protocol Items: Recommendations for Interventional Trials (SPIRIT) [28]. Version 6 of the protocol has been finalised on 7th of January 2020.

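### The SDs meant to size the definitive trial come from raw change scores; the baseline-adjusted residual SD and the baseline/follow-up correlation should be reported beside them

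*Protocol article*

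**What the plan says.** Two sections of the protocol article describe the quantitative comparison. Statistical analysis opens with "Quantitative data will be analysed using descriptive statistics displayed with 95% confidence intervals". It continues with "Changes in outcomes between the intervention arm and control, estimate parameters using means and standard deviations will be descriptively compared", and adds that this will inform the sample size of a full RCT. Outcomes says much the same: "Changes in means and standard deviation will be compared to allow for the sample size calculation for a future trial".

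The trial will hold information that this comparison leaves out. Assessment and outcomes states "Both intervention and control group are assessed at baseline, 3- and 6-month data collection points", and Table 4 schedules the main continuous measures at all three times. Randomisation states "The randomisation will be stratified for hospital site and cancer site (colon or rectum". The article does not mention adjustment for baseline or for the strata, and it does not say how the definitive trial would be analysed.

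**The concern.** This trial tests no hypothesis. The SDs it passes to the full RCT are among its main quantitative products, and the article names the summaries from which they will come: means and SDs of change by arm.

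A change score subtracts the whole baseline value, whereas a regression on baseline subtracts only the part that predicts follow-up. The change score therefore carries extra baseline noise. In a small trial, a chance baseline difference between arms also passes into the difference in change through regression to the mean. Two things are at stake: a planning SD larger than a baseline-adjusted definitive trial would need, and wider intervals in this trial than its data allow.

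**Working it through.** **Inputs from the article.** Allocation is 1:1 (Methods/design: "feasibility parallel group RCT using 1:1 randomisation"). Sample size states "We plan to complete the study with 60 participants allowing for up to 15% drop out over 12 months", with 72 recruited. That total reproduces: 30/0.85 = 35.3, rounded up to 36 per arm, gives 72 (60/0.85 = 70.6, or 71, without rounding by arm). The calculations below use 30 completers per arm.

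**Assumed inputs.** The article gives no baseline/follow-up correlation, so rho is taken over 0.3 to 0.9.

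**Ordering of the two SDs.** With a common within-arm slope b of follow-up on baseline:

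Var(change) = residual variance + (1 − b)² × baseline variance.

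The second term cannot be negative. The change SD is therefore at least the residual SD, with equality only at b = 1. This needs no assumption of equal variances.

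**Size with equal variances.** In units of the outcome variance, Var(change) = 2(1 − rho) and the baseline-adjusted residual variance is 1 − rho². Their ratio, which is also the sample size ratio, is 2/(1 + rho). The CI column compares 95% half-widths at 30 per arm, with t quantiles on 58 and 57 df and a factor √(1 + 1/56) for chance baseline imbalance. The last column is an illustration: difference 0.4 outcome SDs, 90% power, two-sided 5%.

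| rho | SD ratio | Excess N | 95% CI narrower after adjustment | n per arm, change SD vs residual SD |
|---|---|---|---|---|
| 0.3 | 1.24 | 54% | 18.6% | 184 vs 120 |
| 0.5 | 1.15 | 33% | 12.6% | 132 vs 99 |
| 0.7 | 1.08 | 18% | 7.0% | 79 vs 67 |
| 0.8 | 1.05 | 11% | 4.3% | 53 vs 48 |
| 0.9 | 1.03 | 5% | 1.6% | 27 vs 25 |

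**Unequal variances.** With k = baseline SD / follow-up SD, the ratio becomes 1 + (k − rho)²/(1 − rho²). At rho 0.5:
- k = 1: 1 + 0.25/0.75 = 1.33.
- k = 0.7: 1 + 0.04/0.75 = 1.05.
- k = 1.3: 1 + 0.64/0.75 = 1.85.

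The excess can thus be well below or well above the equal-variance figure.

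**Strata.** The number of hospitals is not given, so 2 to 7 stratum terms were tried. If the strata explain none of the residual variance, intervals widen by about 0.1% to 0.4%. If they explain 5% to 10%, intervals narrow by about 2% to 5%.

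**Sampling error of the SD.** On 58 df, the 95% limits of an SD are 0.85 to 1.22 times its estimate.

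**The case against.** The strongest reply is that the article gives a short descriptive summary for a feasibility study, does not call the comparison unadjusted, and may leave covariates to an analysis plan that is not shown. That stands as far as silence goes: the absence of a model is no error. But the article does more than stay silent. It names the summaries and says they feed the next sample size, and a better choice from the same data is open to comment.

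A reader might infer that the planning SD is simply wrong, or that the next trial will be oversized by 18% to 54%. The document supports neither. The change SD is too large only for a baseline-adjusted analysis, and the article does not state the definitive trial's analysis; for an analysis of change it is the matching SD. The 18% to 54% range rests on rho between 0.3 and 0.7 with equal variances. Equal variances are doubtful for guideline adherence, because Table 1 excludes people already following four or more recommendations, which may narrow the baseline spread.

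Nor does the point cover every quantitative outcome. Table 4 collects healthcare use and morbidity only at 6 months, and recruitment, retention and data completion have no baseline value.

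Two further replies have force. For rho of 0.5 or more, the SD inflation (15% or less) is no larger than the sampling error of an SD estimated here; that error, however, is random, while this one always runs in the same direction and can be avoided. Also, the wording under Outcomes could cover SDs at each visit as well as of change. If SDs at baseline (s0), at follow-up (s1) and of change (sd) were all published by arm, then rho = (s0² + s1² − sd²)/(2·s0·s1) and the adjusted SD could be recovered. The article does not commit to all three.

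**Conclusion.** The point holds as a low-cost improvement, not as an error in the trial. For continuous outcomes with a baseline, the planned change-score SD cannot be smaller than the baseline-adjusted residual SD. Sizing a baseline-adjusted definitive trial on it would inflate N by about 54% at rho 0.3, falling to 5% at rho 0.9. This assumes equal variances and a correlation that the article does not give.

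The direction is conservative: the next trial would be larger than needed, not underpowered. There is no excess if that trial analyses change. Baseline adjustment is the substance of the point; the strata terms add little.

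A separate matter bears on both analyses. Recruitment and consent states "Baseline data will be collected following randomisation to the control or intervention arms", so knowledge of allocation could affect baseline values whether they are subtracted or used as a covariate. Adjustment does not cure that.

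**What to change.** Keep the raw means and SDs by arm as descriptive support. For each continuous outcome with a baseline, add the following at 3 and at 6 months:

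- the arm difference with 95% CI from a linear model of the follow-up value on arm, baseline value, cancer site and hospital, with small hospitals pooled;
- the residual SD from that model, with its CI;
- the baseline/follow-up correlation.

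State that the definitive trial will be sized on the SD that matches its planned analysis: the residual SD if it adjusts for baseline, the change SD if it analyses change. Reporting the correlation keeps both routes open.

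The cost is a few lines of Stata and a sentence or two in the analysis plan. No new data are needed, and the hospital terms use only a few degrees of freedom.
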